### 5. Feasibility of the nurse-led delivery

- Feedback from both the participants and therapist on how to adapt this intervention to be delivered by stroke nurses

## Clinical outcomes

Clinical outcomes will be assessed before treatment, immediately after treatment, one-month and three-month after treatment, respectively, including the following measures:

- Fatigue: **Fatigue Assessment Scale** and a **case definition for post-stroke fatigue**
- Depression: **Patient Health Questionnaire-9**
- Independence in daily life: **Nottingham Extended Activities in Daily Living**
- Stroke-specific health-related quality of life: **Stroke Impact Scale**

## Data analysis

Descriptive statistics will be used to analyse the results. An interim analysis will be performed at one-month after the last face-to-face session. The final analysis will be performed at the end of the trial when all data collection, entry and validation are completed (three-month after the last face-to-face session). The data of feasibility will be analysed of a group of 12 participants. The clinical data will be analysed both individually and by group.

The number of participants attending, missing, and withdrawal (from therapy sessions and/or follow up) will be recorded and the relevant rates will be calculated. The success of

recruitment strategies will be measured by summarising responding, eligibility, and consent rated. The feasibility of assessment for clinical outcomes will be determined by the level of missing data of individual items and for the entire outcome questionnaires.

To investigate changes in clinical outcomes, we will report mean change in scores of each questionnaire with 95% confidence interval (CI) from pre-treatment assessment to post-treatment assessment. In addition, the change of scores for each clinical outcome from post-treatment to one-month follow up, and from post-treatment to three-month follow up, will be analysed to determine whether any benefits (if applicable) acquired during the therapy sessions could be maintained one month and three months after the last face-to-face session, respectively.

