### *For clinical outcomes*

6. To test the feasibility of completing questionnaires for clinical outcomes

The secondary objective is to perform a before-and-after analysis of clinical outcomes.

- 1) Fatigue, measured by the Fatigue Assessment Scale (FAS) and by a Case Definition of post-stroke fatigue
- 2) Depression, measured by Patient Health Questionnaire-9 (PHQ-9)
- 3) Independence in daily life, measured by Nottingham Extended Activities of Daily Life (NADL)
- 4) Stroke-specific health-related quality of life, measured by Stroke Impact Scale (SIS)

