### **Participants**

A total of 12 participants will be recruited. Patients who meet all of the following inclusion criteria and do not have any of the exclusion criteria will be eligible for the trial. .

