## **Stage 1: A survey for post-stroke fatigue**

We plan to approach 100 stroke survivors to recruit 12 participants, by supposing a response rate of 50% by the initial contact (the survey for fatigue), 30% of them would be eligible for the trial, and 80% of these eligible people would agree to participate.

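### The group analysis names no change from baseline to one or three months, and judges maintenance from post-treatment changes with no interval or retention criterion stated

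*Protocol*

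**What the plan says.** The clinical analysis is secondary (Aims and objectives, For clinical outcomes): "The secondary objective is to perform a before-and-after analysis of clinical outcomes". Outcomes are collected at four times: before treatment, immediately after it, and one and three months later (Clinical outcomes).

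The Data analysis section opens by calling the analysis descriptive and then fixes three group contrasts. For the first, "we will report mean change in scores of each questionnaire with 95% confidence interval (CI) from pre-treatment assessment to post-treatment assessment". For the other two, "the change of scores for each clinical outcome from post-treatment to one-month follow up, and from post-treatment to three-month follow up, will be analysed". Their purpose is "to determine whether any benefits (if applicable) acquired during the therapy sessions could be maintained one month and three months after the last face-to-face session". No CI, margin or retention criterion is attached to these two.

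Fatigue is "measured by the Fatigue Assessment Scale (FAS) and by a Case Definition of post-stroke fatigue". Step 3 counts the case definition among five questionnaires, so the wording on mean change in scores covers it too.

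On size, "A total of 12 participants will be recruited", in a single arm.

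**The concern.** The objective is a before-and-after comparison, yet at follow-up the named contrasts start after treatment, not before it. They show whether scores moved once therapy ended. They do not directly show how far participants still are from where they began.

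The wording also sets out to determine whether benefit was maintained, using a difference that should be near zero if it was. In 12 people a difference near zero can arise because the gain was kept, or because the estimate is too imprecise to show that it was lost. Without an interval or a criterion, a report could describe an improvement after treatment and its persistence without showing whether the three-month result differs from baseline.

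There is a smaller problem of the same kind. If the case definition sorts people into case and non-case, a mean change in score does not suit it.

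**Working it through.** **1. The plan's own figure.** The section Stage 1: A survey for post-stroke fatigue states: "We plan to approach 100 stroke survivors to recruit 12 participants, by supposing a response rate of 50% by the initial contact", then "30% of them would be eligible for the trial, and 80% of these eligible people would agree to participate". So 100 × 0.50 × 0.30 × 0.80 = 12, which reproduces the stated number. The protocol gives no precision target, SD of change, expected gain or dropout rate. Those below are assumptions, shown as ranges.

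**2. What is named for the group.**

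| Contrast | Named? | 95% CI stated? |
|---|---|---|
| Baseline to post-treatment | Yes | Yes |
| Post-treatment to one month | Yes | No |
| Post-treatment to three months | Yes | No |
| Baseline to one month | No | – |
| Baseline to three months | No | – |

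**3. Can the missing rows be rebuilt?** Let D1 be the change from baseline to post-treatment, and D2 the change from post-treatment to follow-up. For anyone seen at all three visits, baseline to follow-up is D1 + D2, so with complete data the means add. The variance is Var(D1) + Var(D2) + 2 Cov(D1, D2), and the covariance is not among the planned results. If both changes have SD s and correlation ρ, the SD of the sum is s√(2(1 + ρ)):

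- ρ = −0.8: 0.63 s, so half-width at n = 12 is 0.635 × 0.63 s = 0.40 s
- ρ = −0.5: 1.00 s, half-width 0.64 s
- ρ = 0: 1.41 s, half-width 0.90 s

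The same two planned results are thus compatible with quite different intervals. If people drop out, D1 and D2 rest on different people and the means no longer add either.

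**4. Precision of a paired mean change.** The two-sided 95% half-width is t(0.975, n − 1)/√n, in SDs of the change.

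- n = 12: 2.201/3.464 = 0.635
- n = 10 (assumed): 2.262/3.162 = 0.715
- n = 8 (assumed): 2.365/2.828 = 0.836

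**5. Loss not excluded when the observed change after treatment is zero.** This is half-width divided by gain, with the gain taken as known and expressed in SDs of the post-treatment-to-follow-up change. At n = 12:

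| Gain (SD of change) | Largest loss inside the CI, as share of gain |
|---|---|
| 0.5 | 127% |
| 0.8 | 79% |
| 1.0 | 64% |
| 1.27 | 50% |
| 1.5 | 42% |
| 2.0 | 32% |

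Loss of half the gain is just excluded at a gain of 0.635/0.5 = 1.27 SD with 12 people, 0.715/0.5 = 1.43 SD with 10, and 0.836/0.5 = 1.67 SD with 8.

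**6. If half the gain is truly lost.** From the noncentral t distribution at n = 12, the 95% CI for the change after treatment still includes zero with probability 0.88, 0.76, 0.65 and 0.34 for gains of 0.5, 0.8, 1.0 and 1.5 SD of change.

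**7. What the added contrast would deliver.** Its half-width at n = 12 is 0.635 of the SD of its own change score. It estimates the right quantity, but is more precise only if that SD is smaller.

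**The case against.** The strongest reply is that the protocol contains no faulty rule. It calls the analysis descriptive, plans no test, and nowhere says that an interval including zero means benefit was kept. A reader might infer such a rule from the stated aim of determining maintenance, but the text does not contain it. The probabilities in item 6 describe how such a reading would behave, not a planned procedure. This stands. What also stands is that the protocol offers no other criterion.

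A reader might also conclude that change from baseline to follow-up is never examined. That goes too far. Step 5 analyses each participant's baseline, post-treatment and one-month results together, and Step 8 reports the three-month result back to each participant. With complete data the group mean follows by addition. The gap is a named group estimate with its interval.

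Third, the change after treatment does bear on the Step 8 question of whether gains were retained or extended, and a statistical analysis plan could add contrasts. The first part is fair, and is a reason to keep those changes. The second carries less weight, because the protocol itself chose the contrasts and the conclusion to be drawn from them.

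Fourth, it is tempting to say that 12 people cannot exclude loss of most of a gain. That depends on the size of the gain, as item 5 shows, and the protocol gives no figure for it.

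Finally, the protocol does not describe how the case definition is scored. That it yields only case or non-case is a fair inference from its name, no more.

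**Conclusion.** The concern holds in a limited form. At group level, the protocol gives an interval only for baseline to post-treatment. It judges persistence from changes that start after treatment, without an interval or criterion, and omits the contrast that directly measures benefit still present at one and three months. That contrast's interval cannot be obtained from the planned results.

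The size is conditional. With all 12 followed, a change after treatment near zero leaves loss of more than half the gain open when the gain is under about 1.27 SD of change; with 10 followed, under about 1.43 SD. For larger gains it does not. This rests on two-sided 95% t intervals and on assumed values for SD, gain and number followed.

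Severity is minor. This is a secondary, descriptive objective in a feasibility study, and Table 1 reserves effectiveness for the definitive trial. The remark on the case definition holds only if that measure is a yes/no classification.

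**What to change.** In Data analysis:

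- Add, for each scale, the mean change with 95% CI and the number of people contributing, from baseline to one month and from baseline to three months.
- Keep the changes from post-treatment to each follow-up, with 95% CIs, as description.
- Replace the aim of determining whether benefit was maintained with wording about estimating the change from baseline still present at each follow-up, and its uncertainty.
- State how the case definition is scored. If it gives case or non-case, report the number meeting it at each visit and the paired transitions between visits, instead of a mean change in score.

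The cost is a few rows in the results table, from data already to be collected. The change corrects the quantity being estimated. It does not overcome the imprecision of 12 participants, and the report should say so.

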## **Ethics approval**

Trial materials will be reviewed by the South East Scotland Research Ethics Committee, from which an ethics approval will be applied.

A trial sequence number will be allocated to each participant at the beginning of the trial. Identifiable information of participants will be kept on paper in a locked filing cabinet and linked to a trial sequence number. Data retrieved from the trial will be kept in link with the trial sequence number and separate from any identifiable information. All information collected during the course of the study will be kept securely (on paper and electronically) in the Department of Geriatric Medicine of Royal Infirmary of Edinburgh. All the information will be transferred and archived in compliance with the 1998 Data Protection Act.

## **Trial management**

[name] is the Chief Investigator in charge of the overall management of the study, including coordinating with members of the researcher team, promoting the study, collecting of data from participants at different stages of the study, as well as analysing, interpreting, and reporting the results.

[name] and [name], both consultant neurologists, will supervise the trial and provide scientific advice throughout the study. [name], a consultant psychologist, will provide supervision on the delivery process of this brief psychological intervention.

The Sponsor of the study, University of Edinburgh and NHS Lothian, will provide independent oversight of the study to ensure the study is conducted in accordance with good clinical practice.

## Timeline

| Date                                                   | Activities                                                                   | Duration  |
|--------------------------------------------------------|------------------------------------------------------------------------------|-----------|
| January to December 2013                               | Development of the intervention                                              | 12 months |
| January to February 2014                               | Writing protocol                                                             | 2 months  |
| March to May 2014                                      | Application for Ethics approval, R&D approval, and Research Passport         | 3 months  |
| June to August 2014                                    | Recruitment of 12 participants                                               | 3 months  |
| 2 nd June to 30 th November 2014 | Six therapy sessions                                                         | 26 weeks  |
| Up to November 2014                                    | Assessment immediately after treatment                                       | 1 month   |
| Up to December 2014                                    | Assessment one month after treatment                                         | 1 month   |
| December 2014                                          | Interim data analysis                                                        | 1 month   |
| January 2015                                           | Feedback session                                                             | 1 month   |
| February 2015                                          | Feedback meeting with 12 participants
Feedback meeting with the therapist | 1 month   |
| March 2015                                             | Three-month follow up                                                        | 1 month   |
| April to July 2015                                     | Data analysis and report writing                                             | 4 months  |

